#### Concomitant treatments

Concomitant medications or procedures taken concurrently with the study treatment will be listed and summarized by WHO Anatomical Therapeutic Chemical (ATC) Class and Preferred Term. These summaries will include medications starting on or after the start of study treatment, or medications starting prior to the start of study treatment and continuing after the start of study treatment. Prior medications starting and ending prior to the start of study treatment will be listed only.

### Interim analyses {21b}

No formal interim efficacy analysis is planned.

### Methods for additional analyses (e.g., subgroup analyses) {20b}

Additional subgroup analyses will be detailed in the Statistical Analysis Plan.

### Methods in analysis to handle protocol non-adherence and any statistical methods to handle missing data {20c}

Patients will be included in each analysis based on available assessments. No methodology for missing data handling will be applied, except for the EVLWI efficacy endpoint.

### Plans to give access to the full protocol, participant-level data, and statistical code {31c}

These are not applicable.

## Oversight and monitoring

### Composition of the coordinating center and trial steering committee {5d}

The clinical study is coordinated by a professional Clinical Research Organization (CRO). The CRO and the sponsor form the trial steering committee.

The data management is part of the responsibility of the CRO and cannot accessed by the sponsor. No unblinded data are submitted from the data management to the sponsor and to the investigators.

There is no endpoint adjudication committee foreseen.

### Composition of the data monitoring committee, its role and reporting structure {21a}

The sponsor has appointed an independent Data and Safety Monitoring Board. The DSMB’s role is defined in the DSMB Charter of clinical trial EudraCT 2017-003855-47 of March 2018. The DSMB is composed of individual experts in the field of ARDS from the following countries: Germany, Spain, USA. All members of the DSMB have no competing interest in the trial.

The DSMB is responsible for reviewing the safety and tolerability after completion of each dose group and confirmation in writing that the study can proceed with the next higher dose group (dose escalation). After completion of the study, the DSMB will make a final statement concerning overall safety (the primary objective of the study). Overall safety will be assessed in a final session of the DSMB by a summarizing review of the incidence of mortality, adverse events, and serious adverse events, as well as by analysis of relevant laboratory data and ECGs. The DSMB will provide advice to the Sponsor which will be responsible for promptly reviewing the DSMB recommendations, deciding whether to continue, modify, or terminate the trial; and determining whether amendments to the protocol or changes in study conduct are required.

The DSMB is required to act in accordance with the ethical principles derived from the Declaration of Helsinki.

Communication with DSMB members will be primarily through an independent statistician not involved in the management and performance of this study. It is not expected that study investigators or co-investigators will directly communicate with DSMB members.

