## Trial design {8}

This is a Phase IIb, randomized, placebo-controlled, double-blind, dose escalation study. The study will be conducted in up to 10 centers located in Germany and Austria. Additional European countries may be involved.

Thirty eligible patients with pulmonary permeability edema (EVLWI ≥ 10 ml/kg PBW) and moderate to severe ARDS admitted to an intensive care unit (ICU) and under mechanical ventilation will be randomized in a 2:1 ratio to receive either a low dose of solnatide (5 mg) (20 patients) or placebo (10 patients). Patients will be treated for up to 7 days and the study duration for each patient is of up to 28 days.

Following the end of the study period for these patients and prior to escalating from the low dose to the middle dose (60 mg), safety data collected during the 28-day study period will be reviewed by an independent Data Safety Monitoring Board (DSMB), who will decide whether the safety profile is acceptable for dose escalation. In case of positive outcome, 25 new patients will be randomized to solnatide 60 mg or placebo in a 4:1 ratio in order to have 20 patients randomized to the middle-dose group and 5 to the placebo group.

After the end of the study period of these patients and prior to escalating from the middle dose to the high dose (125 mg), safety data will again be reviewed by the DSMB, who will decide whether the safety profile is acceptable for escalating to the high dose.

If so, 40 new patients will be randomized to solnatide 125 mg and placebo in a 1:1 ratio in order to have 20 patients randomized to the high-dose group and 20 patients to the placebo group.

The randomization ratios solnatide/placebo (i.e. 2:1; 4:1; 1:1) will allow to have a total of 35 patients assigned to placebo. In addition, the randomisation schedule will provide the DSMB with enough placebo patients to perform the safety analysis.

To conduct the study, approximately 95 patients will therefore be randomized (see Fig. 1).

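### For the 125 mg step, the first stated by-arm DSMB safety review comes after the trial has ended, too late to protect that step's patients

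*Protocol article*

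**What the plan says.** Two sections of the protocol article fix when the DSMB reviews safety.

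- Trial design {8}, before 60 mg: "safety data collected during the 28-day study period will be reviewed by an independent Data Safety Monitoring Board".
- Trial design {8}, before 125 mg: "After the end of the study period of these patients and prior to escalating from the middle dose to the high dose", the DSMB again reviews safety data.
- Data monitoring committee section {21a}, in general: "The DSMB is responsible for reviewing the safety and tolerability after completion of each dose group".
- The same section, for the end: "After completion of the study, the DSMB will make a final statement concerning overall safety". That statement rests on a final session covering mortality, adverse events, laboratory data and ECGs.

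Neither section states a review within a step. Interim analyses {21b} says that no formal interim efficacy analysis is planned. Section {21a} refers to a DSMB charter of March 2018 for the board's role, and to an independent statistician as the main channel to its members.

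While a step is running, the article provides the following:

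- Every SAE goes to the sponsor within 24 h, and SUSARs go to authorities and ethics committees (Serious adverse event reporting).
- Investigators and pharmacovigilance staff can break individual codes (section {17b}).
- The sponsor can continue, modify or terminate the trial after reviewing DSMB recommendations (section {21a}).
- Data management passes no unblinded data to the sponsor or investigators (section {5d}).

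**The concern.** A review that opens the gate to the next dose protects the patients of the next step. It does nothing for those in the step just finished. For 5 mg and 60 mg the review still informs a later decision within the trial. For 125 mg no further step exists, so the review that would otherwise gate escalation becomes the end-of-trial statement.

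This matters because of the kind of harm to be detected. Deaths and organ failure are common in moderate to severe ARDS. A few more of them on active treatment would look, case by case, like the underlying disease. Single SAE reports, SUSARs (which must be suspected and unexpected) and individual code breaks do not put the arms side by side. Only a tally by arm does that.

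The aim of the trial is to identify safe doses. Under Trial design {8} the 125 mg step combines the highest dose with the best concurrent control: 20 placebo patients, against 10 and 5 in the earlier steps.

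**Working it through.** **Step sizes.** Trial design {8} starts with 30 patients at 2:1 ("Thirty eligible patients with pulmonary permeability edema"), that is 20 active and 10 placebo. In the second step, "25 new patients will be randomized to solnatide 60 mg or placebo in a 4:1 ratio", that is 20 and 5. The third step has 40 patients at 1:1, that is 20 and 20.

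- Total: 30 + 25 + 40 = 95, as stated.
- Placebo: 10 + 5 + 20 = 35, as stated.
- Share of the 125 mg step: 40/95 = 42%.

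**A conflict over the third step.** The randomization section {16a} lists 4:1 for 125 mg. With 20 on solnatide, 4:1 gives 20/4 = 5 placebo patients and a step of 25. The trial total would then be 30 + 25 + 25 = 80, and the first step (30) would be the largest. Sample size {14} gives 20 placebo patients in the high-dose group, in line with 1:1. Under either ratio, at least 20 patients on 125 mg are treated before the first stated by-arm review.

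**Expected deaths in the step.** The Background section cites hospital mortality of 40.3% in moderate and 46.1% in severe ARDS. I use these as stand-ins for 28-day mortality, which is an assumption.

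- 40 × 0.403 = 16.1 and 40 × 0.461 = 18.4, so about 16 to 18 deaths, or 8 to 9 per arm.
- With the wider 34 to 55% also cited there: 40 × 0.34 = 13.6 to 40 × 0.55 = 22.

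**Excess deaths.** No effect on mortality is given, so the excess is assumed.

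- +20 points: 20 × 0.20 = 4 in the whole step, 10 × 0.20 = 2 in its second half.
- +30 points: 20 × 0.30 = 6 and 10 × 0.30 = 3.

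**What a halfway review could show.** Let X (solnatide) and Y (placebo) be independent binomial death counts with n per arm. The chance of a signal is the sum of P(X = x)·P(Y = y) over all pairs (x, y) with one-sided Fisher p at or below the threshold. Placebo mortality is set at 40.3%. The thresholds only measure sensitivity; they are not proposed as rules for action.

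| Assumed excess | 10 v 10, p<=0.10 | 20 v 20, p<=0.10 | 10 v 10, p<=0.05 | 20 v 20, p<=0.05 |
|---|---|---|---|---|
| none | 5% | 5% | 2% | 2% |
| +20 points | 25% | 34% | 13% | 22% |
| +30 points | 42% | 61% | 25% | 46% |

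At 10 v 10, p<=0.10 corresponds to at least 4 more deaths on solnatide than on placebo. With 46.1% placebo mortality and +20 points the p<=0.10 figures are 25% and 36%, so the result hardly depends on the base rate. At p<=0.10 the halfway look keeps 25/34 = 74% (+20 points) or 42/61 = 69% (+30 points) of the sensitivity available at the end, while patients in the step can still benefit.

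**Duration, as a rough guide.** Trial status gives about 4 years: 95/48 = 1.98 patients per month, so 40/1.98 = 20.2 months for a 40-patient step. The 4 years also contain follow-up and the pauses before each escalation, so recruitment while a step is open would be faster and the step shorter. This is an average, not an accrual forecast.

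**The case against.** **The charter is not shown.** The article refers to it for the DSMB's role, and ad hoc meetings or within-step data packages are what such a charter would settle. A condensed article need not repeat them. This stands in part: it cannot be said that the DSMB has no other reviews. But the article does not leave the timing open. It states the review points in two sections, and for the last step they fall after the trial.

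**A reader might infer that an excess of deaths could not stop the 125 mg step.** The documents do not support that. SAEs reach the sponsor within 24 h whatever their suspected cause, pharmacovigilance staff can break codes, the sponsor can terminate, and nothing bars an unscheduled DSMB meeting. What is missing is a planned look that would bring an imbalance to light.

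**A reader might also take it as stated that the DSMB sees unblinded data.** It is an inference from the independent statistician and from the remark in Trial design {8} that the allocation gives the DSMB enough placebo patients for its safety analysis.

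**The dose is not new.** The article reports two earlier phase II trials (40 and 20 patients, both 1:1, so about 30 on solnatide) and says that 125 mg twice daily was used. The first found no significant difference in adverse events that the underlying diseases could not explain. The second reported no drug-related adverse events and no deaths. This lowers the prior concern. About 30 treated patients do not settle the question, and this trial still has identifying safe doses as its aim.

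**The mortality inputs are soft.** They are hospital figures, and the trial excludes patients not expected to survive 48 h or the next month. That is fair, and is why a range is shown.

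**One halfway look would usually miss a 20-point excess.** True: about 75% of the time at p<=0.10. Because recruitment continues while outcomes mature, fewer than half the exposures would remain. The end-of-step review is not much more sensitive, though, and it comes when nobody in the step can benefit.

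**Conclusion.** The point holds as one about timing. The article states DSMB safety reviews after each completed dose group and at the end of the trial. For 125 mg these coincide, so at least 20 patients are treated at the highest dose before any stated comparison by arm. The other safeguards are real, but they work case by case and cannot show an excess of expected deaths.

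The size is moderate. With an assumed 20- to 30-point excess, 4 to 6 extra deaths would accrue in the step, of which 2 to 3 fall in its second half. A halfway review would give a signal (one-sided Fisher p<=0.10) with probability 25% to 42%. These figures rest on 1:1 allocation with 20 per arm, on hospital mortality standing in for 28-day mortality, and on assumed excesses. That the first stated review of the 125 mg step comes too late does not depend on them. This is an inexpensive improvement to a stated schedule. It does not show that the trial lacks safety oversight.

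**What to change.** 1. Reconcile the size and ratio of the third step between Trial design {8} with Sample size {14} and the randomization section {16a}. The midpoint depends on it: about 10 v 10 under 1:1 with 40 patients, but only about 10 v 2 or 3 under 4:1 with 25, where a comparison would say much less.
2. Add to Trial design {8} and to section {21a} one scheduled DSMB review about halfway through the 125 mg step, covering deaths, SAEs and treatment discontinuations by arm. The independent statistician prepares it, recruitment continues meanwhile, and no efficacy data are shown, so no alpha is spent.
3. If the charter already provides such a review, align the two sections with it.
4. Leave the criteria for action to the charter.

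The cost is one extra data package, one DSMB meeting and, if needed, a charter update. No patients or procedures are added. The DSMB should know the limited sensitivity in advance, so that an unremarkable halfway look is not read as evidence of safety.

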### Adverse event reporting and harms {22}

All identified non-serious AEs (related and unrelated) must be recorded and described on the non-serious AE page of the eCRF.

#### Serious adverse event reporting

Every SAE, regardless of suspected causality, occurring after screening and until at least 28 days after randomization must be reported to the sponsor within 24 h of site awareness. Any SAE experienced after this 28-day period should only be reported to the sponsor if the investigator suspects a causal relationship to the study treatment. Recurrent episodes, complications, or progression of the initial SAE must be reported as follow-up to the original episode within 24 h of the investigator receiving the follow-up information. Information about all SAEs will be recorded on the AE page of the eCRF and transmitted through the SAE tool. In case of technical difficulties, SAE notification can be carried out by sending a paper SAE form to the Pharmacovigilance Officer via email or by fax.

All SAEs still ongoing at end of study will be followed up by means of queries requesting updates. Other supporting documentation of the event may be requested by the study sponsor and should be provided as soon as possible. The study sponsor will be responsible for notifying Health Authorities of any unexpected fatal or life-threatening suspected adverse reaction as soon as possible, but in no case later than 7 calendar days after the sponsor’s initial receipt of the information.

Suspected unexpected serious adverse reactions (SUSARs) will be collected and reported to the competent authorities and relevant ethics committees in accordance with Directive 2001/20/EC or as per national regulatory requirements in participating countries.

#### Reporting events to participants

Should an event occur that changes the overall benefit/risk ratio of the study, the Sponsor shall evaluate if a risk minimization measure is needed. Should this measure require a substantial amendment to the protocol, the informed consent and patient information will be revised and submitted to the patient for written consent.

### Frequency and plans for auditing trial conduct {23}

Clinical site monitoring will be conducted to ensure that the rights and wellbeing of human subjects are protected, that the reported study data are accurate, complete, and verifiable, and that the conduct of the study complies with the currently approved protocol, with Good Clinical Practice (GCP), and with applicable regulatory requirements. Monitoring for this study will be performed by a Contract Research Organization (CRO), OPIS. Details of clinical site monitoring are documented in a Monitoring Plan (MP). The MP describes in detail who will conduct the monitoring, at what frequency monitoring will be done, at what level of detail monitoring will be performed, and the distribution of monitoring reports. Further audits are at the discretion of the respective authorities in charge of overseeing medicinal products trials.

### Plans for communicating important protocol amendments to relevant parties (e.g., trial participants, ethical committees) {25}

Important protocol modifications will be reported to the responsible ethics committees and, after approval, made accessible to the study centers. As far as the ICF is subject to any revision, all future participants will be provided with an updated version of the ICF. Protocol amendments will not be communicated to past participants.

## Dissemination plans {31a, b, c}

This study will ensure that the public has access to the published results of the research. The International Committee of Medical Journal Editors (ICMJE) member journals have adopted a clinical trials registration policy as a condition for publication. The ICMJE defines a clinical trial as any research project that prospectively assigns human subjects to intervention or concurrent comparison or control groups to study the cause-and-effect relationship between a medical intervention and a health outcome. Medical interventions include drugs, surgical procedures, devices, behavioral treatments, process-of-care changes, and the like. Health outcomes include any biomedical or health-related measures obtained in patients or subjects, including pharmacokinetic measures and adverse events. The ICMJE policy requires that all clinical trials be registered in a public trials registry such as ClinicalTrials.gov, which is sponsored by the National Library of Medicine. Other biomedical journals are considering adopting similar policies.

Access to participant-level datasets and statistical code can be granted upon request to the sponsor’s discretion.

## Discussion

This protocol describes the process of a Phase II clinical trial investigating the safety of a novel inhaled agent for the treatment of moderate to severe ARDS. In addition to the challenges one faces with every pharmaceutical investigation, this study has some peculiarities which shall be discussed here briefly.

The route of administration of the IMP is bronchial inhalation. One major advantages of this way of administration is the possibility to bring the IMP straight to the desired site of action (i.e., the lungs) with minimal plasmatic absorption, depending on the agent’s pharmacokinetic properties. The latter was shown for solnatide in a first-in-man study [22], which may indicate a low risk of undesired systemic effects. However, inhalative administration, unlike intravenous or oral use, is fraught with some degree of variation in terms of the amount of agent that actually reaches the alveolae. This is due to each individual’s anatomical and physiological features of the respiratory tract and has been addressed systematically in earlier research [33]. To minimize this effect as best as possible, standardization of the procedures is key. Therefore, all patients in this study will be treated using the same model of bronchial inhaler and great care was taken to make the setup of the respirator, tubes, suction devices, and tubes as similar as possible between patients and study centers.

Another issue to keep in mind is the relatively narrow timeframe for inclusion of a patient. The protocol requires a diagnosis of moderate to severe ARDS not older than 48 h, yet the patient needs to be stable in this condition for at least 8 h. In practice, potential study patients will initially often be treated in peripheral hospitals, deteriorate there until they meet the required criteria, and then be transferred to one of the study centers for further treatment in a more or less unstable condition. Therefore, once the patient is stable enough to be enrolled in the trial, there will possibly be only little time left to get informed consent and have all data necessary for inclusion ready. In order to respond to this challenge, proper preparation of the required examinations and procedures is advised. Also, determination of the exact point in time of the ARDS diagnosis is key. Respiratory deterioration alone does not fulfill the Berlin criteria definition of ARDS, so technically, the 48 h from diagnosis until possible enrolment will frequently not start until appropriate chest imaging was performed.

The patient’s possible need for extracorporeal membrane oxygenation (EMCO) therapy during the course of the intervention phase of the trial should also be considered early on. While ECMO therapy at screening leads to exclusion of the patient, once a patient is enrolled, extracorporeal therapy will be initiated as is clinically appropriate. This is, for ethical reasons, not to be disputed. However, quality of the collected data will be compromised in patients on ECMO therapy during the first 7 days of the trial. In particular, extravascular lung water (index) was found to be estimated significantly higher in such patients due to the altered hemodynamics caused by the extracorporeal circuit [34]. The responsible investigator will have to make an individual decision for every patient about to be included in the trial, considering both quality of data on the one hand and potential selection bias against the most severely sick patients on the other hand.

A last point to consider might be the fact that basically all patients will be unable to give informed consent themselves at the time of screening. Inclusion criteria demand that any patient needs to be mechanically ventilated at screening, and this will usually go along with the use of some form of sedative medication. So, having the procedures for enrolling such patients in place according to local legal requirements must be taken care of beforehand. Moreover, it is assumed that patients will be hospitalized in the study facility over the entire course of the observational period due to the severity of their conditions. In case a patient is transferred sooner than 28 days after enrolment, individual measures need to be found in order to ensure data assessment.

We present here the protocol for a randomized, double-blind, parallel-group clinical trial investigating the safety of a novel inhaled agent for the treatment of pulmonary permeability edema in patients with moderate to severe ARDS. As was laid out, especially during screening and the intervention phase (days 0 to 7), the coordination of tasks and procedures can be demanding at times. However, with proper preparation of the required processes and some consideration of the possible pitfalls discussed above, reliable, high-quality data can be collected throughout the 28-day intervention and follow-up period.

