#### Exclusion criteria

Patients must meet none of the exclusion criteria listed below.
History of clinically relevant allergies or idiosyncrasies to solnatide.Known use of any other investigational or non-registered drug within 30 days or within 5 half-lives of these drugs prior to study enrolment, whichever is longer. No exceptions are allowed in this study.Severe state of septic shock with a mean arterial pressure (MAP) ≤ 65 mmHg and a serum lactate level > 4 mmol/L (36 mg/dl) despite adequate volume resuscitation.An underlying clinical condition that, in the opinion of the investigator, would make it very unlikely for the patient to be successfully weaned from ventilation due to severe underlying diseases (e.g., severe malnutrition, severe neurological diseases, pulmonary fibrosis, or COPD).Extracorporeal membrane oxygenation, high-frequency oscillatory ventilation or any form of extracorporeal lung support. In no way are patients to be denied or delayed these procedures to avoid exclusion from the study.Neutrophil count < 0.3 × 10^9^/L.Cancer treatment (chemotherapy or biological) or therapy with other immunosuppressive agents for organ transplantation within 2 weeks.Cachexia (BMI < 18.5 kg/m^2^).Unequivocal cases of cardiogenic pulmonary edema (if differential diagnosis based on an ARDS triggering condition and clinical replicability is not possible, echocardiography may be indicated).Severe skin burns involving more than 15% of body surface.Subjects who are extremely unlikely to survive more than 48 h due to the acute conditions of the patient in the opinion of the investigator.Subjects transferred from a hospital not participating in this study who are already planned to be re- transferred during the observation period.Subjects who are not expected to survive the next month because of an underlying uncorrectable medical condition or a do not resuscitate order.Women known to be pregnant, women who are lactating, women with a positive or indeterminate pregnancy test, on screening, and males of reproductive potential and women of childbearing potential who are not willing to use highly effective methods of birth control/contraception for a duration defined in the patient’s Informed Consent Form.After randomization, drop-out of a participant is not envisaged by the protocol except for withdrawal of consent by the participant or his/her legal representative, discontinuation of the treatment (e.g., due to toxicity, or death of the patient during the treatment course).

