## Statistical methods

### Statistical methods for primary and secondary outcomes {20a}

Data collected in this study will be listed and summarized as described below by treatment group. Data from all sites will be pooled and summarized. Continuous data will be summarized by mean, standard deviation (SD), median, first and third quartiles, minimum, and maximum. Categorical data will be presented by absolute and relative frequencies (n and %) or contingency tables. All statistical tables, listings, figures, and analyses will be performed by means of SAS® release 9.4 or later (SAS Institute, Inc., Cary, NC, USA).

A two-sided alpha level 0.05 will be considered. No alpha level adjustment will be made for secondary preliminary efficacy outcome variables and for multiple comparisons. Patients will be included in each analysis based on available assessments. No methodology for missing data handling will be applied, except for the EVLWI efficacy endpoint. Censoring rules for time-to-event analyses will be detailed in the Statistical Analysis Plan.

There is no primary efficacy endpoint as the primary objective of the study is to investigate the safety of solnatide. All efficacy analysis will be considered as secondary preliminary efficacy analyses. All secondary preliminary efficacy analyses will be performed based on the ITT set as primary analysis and on the PP set as supportive analysis and will be reported by planned treatment cohort.

No methodology for missing data handling will be applied for secondary preliminary efficacy endpoints, except for EVLWI. The homogeneity of treatment effects across different centers will not be tested.

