#### Change from baseline to day 7 in extravascular lung water index (EVLWI)

The absolute change from baseline in extravascular lung water index (EVLWI) after 7 days from randomization, as assessed with a validated bedside measurement (single indicator transpulmonary thermodilution measurement, such as with PiCCO® from Pulsion or VolumeView from Edwards), will be analyzed by means of an analysis of covariance (ANCOVA) model with baseline value as covariate and treatment cohort as an independent class variable. Mean estimates will be provided, together with their corresponding two-sided 95% confidence intervals.

A hierarchical testing procedure will be carried out to control multiplicity, where statistical comparison will first be performed between the highest solnatide dose cohort and the placebo cohort. Statistical comparison between the next lower dose(s) and placebo will be performed only in case of statistical significance of the comparison between the highest solnatide dose cohort and the placebo cohort.

The analysis described above will be performed on data where the Last Observation Carry Forward approach is applied for handling missing data. Additional imputation methodologies for missing data may be applied as sensitivity analysis (further details to be provided in the Statistical Analysis Plan).
Secondary preliminary efficacy endpoints

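### The plan says EVLWI reads too high on ECMO, yet its day-7 EVLWI analysis makes no exception for such readings, and the Discussion adds an inclusion judgement that no eligibility criterion covers

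*Protocol article*

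**What the plan says.** **ECMO and eligibility.** The Exclusion criteria list "Extracorporeal membrane oxygenation, high-frequency oscillatory ventilation or any form of extracorporeal lung support". The Discussion adds: "While ECMO therapy at screening leads to exclusion of the patient, once a patient is enrolled, extracorporeal therapy will be initiated as is clinically appropriate". Baseline is therefore off ECMO, while a later reading may be on it.

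**The measurement problem.** The Discussion states that "quality of the collected data will be compromised in patients on ECMO therapy during the first 7 days of the trial", and that "extravascular lung water (index) was found to be estimated significantly higher in such patients due to the altered hemodynamics caused by the extracorporeal circuit".

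**The analysis.** Day-7 change in EVLWI is analysed with an "analysis of covariance (ANCOVA) model with baseline value as covariate and treatment cohort as an independent class variable". The ITT set is primary and the PP set supportive. Last observation carried forward (LOCF) is applied to missing values. The general rule in Statistical methods {20a} is "Patients will be included in each analysis based on available assessments". The SAP is to supply censoring rules, possible further imputation methods as sensitivity analyses, and subgroups. Use of extracorporeal treatments is recorded as a safety parameter (Outcomes {12}).

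**The response offered.** The Discussion's answer to the ECMO problem is at inclusion, not in the analysis: "The responsible investigator will have to make an individual decision for every patient about to be included in the trial". It asks the investigator to set data quality against the risk of selecting against the sickest patients.

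**The concern.** The plan identifies a measurement artefact with a known direction, in the window of its key preliminary efficacy endpoint, and then fixes a main analysis that does not mention it. An off-ECMO baseline compared with an on-ECMO day-7 value makes a patient appear to have cleared less lung water than is the case. LOCF can extend this to a patient whose day-7 value is missing and whose last reading was on ECMO.

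Two things are at stake. The first is the EVLWI comparison: it loses precision in any event, and it is exposed to bias if ECMO use differs between the groups compared. The highest dose against placebo is tested first and the lower doses only if that test succeeds, so a loss of power there affects the whole sequence. The second is the population. A case-by-case judgement about likely ECMO need, outside the listed criteria, can change who is enrolled and cannot be reconstructed afterwards unless the reasons are recorded.

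**Working it through.** **Inputs from the protocol article (Sample size {14}).** 20 evaluable patients per group, difference 3.2 ml/kg, common SD 3.5, two-group t-test, two-sided 0.05, power of approximately 80%.

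**Inputs assumed.** The article gives the direction of the ECMO effect on EVLWI but not its size, and gives no ECMO rate. I take a shift *b* of 2 to 10 ml/kg and, unless stated otherwise, a share *q* of 10% of patients whose analysed day-7 value is an on-ECMO reading.

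**Step 1: the plan's own figure.** Exact power from the noncentral t distribution with 38 degrees of freedom is 80.4%. The stated 80% reproduces, so the power calculation is not at fault.

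**Step 2: equal ECMO use in both groups.** The artefact cancels in the difference of means but adds variance:

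SD = √(3.5² + q(1 − q)b²)

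With q = 0.10, q(1 − q) = 0.09, and 3.5² = 12.25:

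| Shift b (ml/kg) | SD | Power for 3.2 ml/kg |
|---|---|---|
| 0 | 3.50 | 80.4% |
| 2 | √(12.25 + 0.36) = 3.55 | 79.3% |
| 5 | √(12.25 + 2.25) = 3.81 | 73.6% |
| 6 | √(12.25 + 3.24) = 3.94 | 70.7% |
| 10 | √(12.25 + 9.00) = 4.61 | 57.1% |

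Contrast bias is 0 and type I error stays at 5%. At 30% use in both groups and a shift of 6 ml/kg, power is 60.1%.

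**Step 3: unequal ECMO use.**

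Bias in the contrast = b × (share on placebo − share on solnatide)

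A positive value favours solnatide. With 20 per group, 10 percentage points is two patients.

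- Per 10 points: 2 × 0.10 = 0.2 ml/kg up to 10 × 0.10 = 1.0 ml/kg, or 6% to 31% of the 3.2 ml/kg design difference.
- Solnatide 10%, placebo 30%, shift 2 to 6: bias of 0.4 to 1.2 ml/kg in favour of solnatide. The rejection rate under no effect is 6.4% to 14.2%.
- Solnatide 30%, placebo 10%, shift 2 to 6: the same bias against solnatide. Power is 67.3% to 31.1%.

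These figures use an unadjusted t-test as an approximation to the ANCOVA. They also treat the SD of 3.5 as free of ECMO variance, which cannot be checked from the article.

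**Step 4: the inclusion judgement.** The Exclusion criteria cover current extracorporeal support. No inclusion or exclusion criterion covers expected need for it. Study setting {9} and Recruitment {15} have every ARDS patient at the sites evaluated or screened. The Discussion nevertheless asks for an individual decision on each patient. That decision precedes concealed allocation (Sequence generation {16a}), so within a dose step it affects who is enrolled, not how the arms compare.

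**The case against.** **No sentence says on-ECMO readings are kept.** This is correct. The available-assessments rule speaks of patients and sits with the missing-data text; it does not rule on whether a compromised reading is valid. The SAP or the PP definition, neither shown, might deal with it. What stands against this is that the main EVLWI model, its analysis set and its LOCF rule are all fixed in the article. What is deferred for this endpoint is additional imputation as an optional sensitivity analysis. Followed as written, the plan uses the readings by default, and where it raises the artefact it responds with a decision at inclusion.

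**A reader might infer that the EVLWI comparison is biased.** The documents do not support that. An affected patient's change score is wrong, but the contrast is biased only if ECMO use differs between the groups compared, and nothing in the article shows that it will.

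**The size is assumed.** This stands. At 10% use and a 2 ml/kg shift, power falls by about one percentage point.

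**The inclusion text is commentary.** It neither orders exclusion nor adds a criterion, and the listed criteria already rely on investigator opinion in places. That limits the point. A reader might also infer that the sickest patients will be removed unevenly across sites, or that the arms will become unbalanced. The first is possible but not shown; the second does not follow within a step.

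**Deleting on-ECMO readings is not clearly better.** This stands. ECMO start follows randomisation and is tied to deterioration, so such missingness is informative. The protocol has no repeated-measures model to absorb it, and LOCF would substitute a pre-ECMO value.

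**Conclusion.** The concern holds in a limited form. The article acknowledges that EVLWI is overestimated on ECMO and fixes a day-7 analysis that neither excepts nor examines those readings. The direction of the error in an affected patient comes from the article itself. The consequence for the trial rests on an assumed ECMO share and shift: with equal use at 10%, power between about 79% and 57%; with unequal use, 0.2 to 1.0 ml/kg in the contrast per 10 points, in either direction. The documents establish exposure to bias, not bias.

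The inclusion judgement can alter the enrolled population but does not disturb arm balance within a step. Only if it drifted between the sequential steps could a comparison using placebo combined across steps be affected.

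Safety is the main objective, there is no primary efficacy endpoint, and the sample size rests on feasibility. The change is worth making because EVLWI is the key preliminary efficacy endpoint and the fix is cheap, but it does not undermine the trial.

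**What to change.** 1. Prespecify at least one sensitivity analysis of day-7 EVLWI in which on-ECMO readings are neither taken at face value nor carried forward. One example is a rank-based comparison with ECMO start or death ranked as the worst outcome.
2. State explicitly how on-ECMO readings enter the main ANCOVA. If they are dropped, justify it and say what replaces them, since the missingness is informative.
3. Report ECMO use by arm and by day, so that a reader can judge whether the contrast is exposed.
4. Reconcile the Discussion with the eligibility criteria so that inclusion follows written criteria, and log reasons for non-inclusion. Whether expected ECMO need belongs among those criteria is for the sponsor and investigators.

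The cost is some wording and a little extra analysis. Extracorporeal treatment is already recorded as a safety parameter; the screening log would need a reason field if it lacks one.
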